## Abstract

**Objective::**

To explore the effect of management of nursing case on blood pressure control in hypertension patients.

**Method::**

This is a randomized controlled study which will be carried out from May 2021 to May 2022. The experiment was granted through the Research Ethics Committee of the People's Hospital of Chengyang District (03982808). Our research includes 200 patients. Patients who meet the following conditions will be included in this experiment: the patients aged 18 to 60 years; the patients had the diagnosis of hypertension; and the urban residents. While patients with the following conditions will be excluded: having renal failure, liver failure, heart and respiratory failure; and known pregnancy. Primary result is blood pressure, while secondary results are treatment compliance, waist circumference, body mass index (BMI), type and number of antihypertensive agents used, and the existence of metabolic and cardiovascular comorbidities.

**Results::**

Table 1 shows the clinical outcomes between the two groups.

**Conclusion::**

Nursing case management is effective to improve the prognosis of hypertension patients.

## Introduction

1

Hypertension is one of the cause of death worldwide, which is preventable.^[1,2]^ It is also a significant risk factor for myocardial infarction, heart failure, stroke, as well as other serious renal and cardiovascular diseases.^[3–5]^ The incidence rate of hypertension rises with the age of adults. It is reported that 36% of the adults aged 40 to 64 suffer from hypertension; among adults aged 65 and above, the proportion has increased to 70%.^[6,7]^ It has become a serious problem of public health. Since the hypertension is asymptomatic, its detection and control remains a challenge. The hypertension patients are managed via the primary health care provider.^[8]^ Nevertheless, although the progress has been made in the management of chronic diseases, the hypertensive patients who receive regular treatment from primary care providers do not meet their targets of blood pressure.

In recent years, more and more researches begin to pay attention to the significant role of the management of nursing case in treating hypertension.^[9,10]^ It requires a complex care, involving major lifestyle changes such as adherence to medication, reduced salt intake, the measurement of blood pressure and exercise. Nevertheless, the hypertension patients have poor self-management behaviors. The self-care and self-efficacy behavior of uncontrolled hypertension patients are lower. Case management is a kind of healthcare strategy that determines patients at high risk, prevents complications and disease progression, and promotes the patients participation in self-care. Other targets involve caring for the perspectives and needs of patients, developing personalized care programs, improving the quality of health care, and decreasing decentralized patient care. The former researches have suggested that management of case may have a positive effect on hypertension.^[11–13]^ In addition, it can increase the knowledge about the disease; adhere to the treatment plans and help the patients improve their own lifestyle. Although it has achieved positive results in the case management of chronic disease, it has not been applied in patients with hypertension. Hence, we conduct the randomized controlled study protocol to explore the effect of management of nursing case on blood pressure control in hypertension patients.

## Materials and methods

2

This is a randomized controlled study which will be carried out from May 2021 to May 2022 at the People's Hospital of Chengyang District. The experiment was granted through the Research Ethics Committee of the People's Hospital of Chengyang District (03982808) and recorded in research registry (researchregistry6244).

### Inclusion criteria and exclusion criteria

2.1

Patients who meet the following conditions will be included in this experiment: the patients aged 18 to 60 years; the patients had the diagnosis of hypertension; and the urban residents. While patients with the following conditions will be excluded: having renal failure, liver failure, heart and respiratory failure; and known pregnancy. All the patients are randomly assigned to the random number through utilizing a random-number table, and the result of distribution is kept in a random envelope and is invisible. All the patients are randomly divided to the control group and study group, and there are 100 patients in each group.

### Nursing case management

2.2

The nursing standards of the control group are as follows: renewal of prescriptions in meetings, free distribution of hypertension medication, and the monitor of blood pressure every 2 months, nursing and medical appointments, and consultation with psychologists and nutritionists based on the needs of patients.

In intervention group, patients are given management of nursing case. From the existing management activities, the arrangements are as follows: telephone contacts, nursing consultations, personal health education activities, and home visits. The nursing consultations are implemented every 6 months. The purpose of the consultation is to gather information that can be utilized to draft personal care plans and to set mutually agreed targets. The consultation lasts about an hour, involving the targeted health education, the measurement of waist circumference and blood pressure, and the calculation of BMI. Telephone contact is conducted every 1 month to reassess the healthcare plans of patients and remind the patients to consult the agendas in a timely manner. WeChat is a kind of instant messaging tool, which allows the voice calls through using the mobile phone, and it is also utilized for communication. Each telephone meeting lasts about 10 min. In the process of home visits, the case manager will observe the home environment, for instance, the living conditions and family's interaction. They offer the health education, check the weight of patient and their blood pressure, and then review the targets and medical plans. All the verbal instructions will be recorded and the patients will be provided the copy for consultation if needed. For the home visits, it lasts about 45 min. And the group activities contain the interactive activities and informational lectures. The focus of these activities is to develop healthy habits. The theme of educational activities is selected according to patients’ main needs. The activities of collective health education are carried out in community space. These group activities last about 1 h. Personalized educational activities are offered in the process of nursing consultation, telephone consultation, and home visit. All information acquired in the process of nursing management will be recorded.

### Outcomes

2.3

Primary result is blood pressure, while secondary results are treatment compliance, waist circumference, BMI, type and number of antihypertensive agents used, and the existence of metabolic and cardiovascular comorbidities.

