### Statistical analysis

2.4

The analysis of all the data are conducted with the software of IBM SPSS Statistics for Windows, version 20 (IBM Corp, Armonk, NY). Afterwards, all the data acquired are represented through the appropriate characteristics, for example, standard deviation, and mean, median as well as percentage. And independent *t* tests and χ^2^-tests are respectively utilized to analyze the categorical variable and continuous variable. *P* value < .05 indicates that there is statistical significance.

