## Result

3

Table 1 shows the clinical outcomes between the two groups.

**Table 1 T1:** The clinical outcomes between the two groups.

Outcomes	Study group	(n = 100)	Control group (n = 100)	*P*
Systolic blood pressure				
Diastolic blood pressure				
Mean arterial pressure				
Waist circumference				
Body mass index				
Quality of life score				

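### The primary outcome is named only as blood pressure, with three separately tested candidate measures and no rule for choosing among them; if any one sufficed, the false-positive rate would be about 7% to 10.5% rather than 5%

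*Protocol article*

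**What the plan says.** All references are to the protocol article.

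- **Section 2.3, Outcomes:** "Primary result is blood pressure". The Abstract (Method) says the same. Neither gives a component of blood pressure or an assessment time.
- **Section 3, Table 1:** an empty results table with rows for "Systolic blood pressure", "Diastolic blood pressure" and "Mean arterial pressure", among others, under a single P column. No row is marked as primary.
- **Section 2.4, Statistical analysis:** one threshold for everything, a P "value < .05 indicates that there is statistical significance". No order of testing, adjustment or joint criterion is given, and sidedness is not stated. The tests are the t test and the chi-squared test, "respectively utilized to analyze the categorical variable and continuous variable". That pairing is the wrong way round; I take the t test as the one meant for blood pressure.
- **Section 2.1:** "there are 100 patients in each group".

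**The concern.** A 5% threshold gives a 5% chance of a false primary claim only when there is one primary test. Here the primary outcome is a heading that covers three measures, each with its own P value judged at .05. As written, the plan would not stop the investigators from reporting whichever measure crossed the threshold as the primary result. It also gives no rule for the conclusion if systolic and diastolic pressure disagree. Mean arterial pressure is conventionally calculated from the other two, so it adds a further test with almost no new information.

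What is at stake is the meaning of a positive result. A reader could not tell whether the reported measure was chosen before or after the data were seen.

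**Working it through.** **The document's own figure.** The only figure is the .05 threshold. For a single primary test, 1 - 0.95 = 0.05, so it holds as stated for one measure. No error rate across measures is given.

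**Inputs.**
- Three measures, each with a P value (Table 1); threshold .05 for each (section 2.4).
- Two-sided testing: assumed.
- Mean arterial pressure, MAP = (SBP + 2 x DBP)/3: assumed; the article gives no formula.
- Systolic-diastolic correlation r: not given; range 0.3 to 0.9 assumed.
- SDs: not given; 15 and 10 mmHg assumed (ratio 1.5), with ratios 1.2 to 2.0 also tried.
- The 100 patients per group do not affect a false-positive rate.

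**Bounds that do not apply.** Three independent tests would give 1 - 0.95^3 = 14.3%, and the Bonferroni bound is 3 x 0.05 = 15%. Both overstate the rate, because MAP is a combination of the other two and all three are correlated.

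**Correlated calculation.** With no true effect, take z1 for SBP and z2 for DBP as standard normal with correlation r. Then

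z3 = (15 z1 + 2 x 10 z2) / sqrt(15^2 + 4 x 10^2 + 4 r x 15 x 10).

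At r = 0.6 the denominator is sqrt(225 + 400 + 360) = 31.38. MAP then correlates (15 + 12)/31.38 = 0.86 with SBP and (9 + 20)/31.38 = 0.92 with DBP.

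The table gives the chance of at least one significant result (critical value 1.96; 2,000,000 draws, Monte Carlo standard error about 0.02 points). Direct numerical integration agrees to within 0.02 points.

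| r | SBP, DBP or MAP, either direction | SBP or DBP only, either direction | SBP, DBP or MAP, benefit only |
|---|---|---|---|
| 0.3 | 10.51% | 9.53% | 5.26% |
| 0.4 | 10.11% | 9.34% | 5.05% |
| 0.5 | 9.66% | 9.08% | 4.83% |
| 0.6 | 9.17% | 8.76% | 4.59% |
| 0.7 | 8.61% | 8.35% | 4.30% |
| 0.8 | 7.94% | 7.80% | 3.97% |
| 0.9 | 7.08% | 7.03% | 3.53% |

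The reference value is 5% for the first two columns and 2.5% for the last. SD ratios from 1.2 to 2.0 move the first column by at most 0.1 point.

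**Where the excess comes from.** At r = 0.3 the excess over 5% is 5.51 points, of which systolic plus diastolic give 4.53 (82%). At r = 0.9 it is 2.08 points, of which they give 2.03 (98%).

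**With a rule in place.**
- One named measure: 5%.
- Diastolic tested only after a significant primary: with no effect on either, a false claim needs a false first result, so 5%.
- All three required: at most 5%.
- Bonferroni at 0.05/3 = 0.0167 each: at most 5%.

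**The case against.** **No success rule is stated.** Section 2.4 says when a P value is called significant, not when the trial is positive. If all measures had to be significant, the error would be at most 5%. This stands. A reader might infer that the plan runs at about 8% to 10% as a fact; the article does not support that, because the figure needs an any-one-suffices rule that it neither states nor excludes, and a correlation that it does not give.

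**Table 1 is weak evidence of what is primary.** It is an empty shell that does not match section 2.3: it adds a quality of life score and omits treatment compliance, antihypertensive agents and comorbidities. This stands in part. That all three pressure rows are primary is an inference. But systolic and diastolic are both blood pressure on any reading, and those two alone give 7.0% to 9.5% under the same rule.

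**The objective is not measured.** Because the objective refers to "blood pressure control in hypertension patients", a reader might infer that a proportion reaching a target is missing. The documents do not support this. The phrase can mean the level of blood pressure, and absence from a table that omits other declared outcomes proves little. Adding such an outcome would be a preference.

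**An analysis plan may settle it.** Test order and adjustment are commonly left to a document not shown here. That is fair for those details. It does not cover the primary variable itself, which the article states and leaves open.

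**Conclusion.** The point holds in conditional form. The article declares a primary outcome without saying which blood pressure measure it is, assigns separate P values to three candidates, applies .05 to each, and does not select, order or combine them.

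If any one were allowed to count as primary success, the two-sided false-positive rate would be about 7% to 10.5% instead of 5%, and the rate of false claims of benefit about 3.5% to 5.3% instead of 2.5%. These figures rest on an assumed correlation of 0.9 to 0.3 and the assumed MAP formula; they barely depend on the SDs. The number of rows matters less than the choice between systolic and diastolic.

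I rate this as should-fix, not must-fix: the gap in the definition is certain, but the inflation depends on a decision rule that the article does not state.

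**What to change.** In section 2.3, name one primary measure, for example systolic pressure, at one pre-specified time after randomisation that is the same in both groups. The common time needs stating because section 2.2 describes different contact schedules: monitoring every 2 months in the control group, and 6-monthly consultations plus home visits in the intervention group.

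In section 2.4, state that this measure is tested at two-sided 5%, that diastolic pressure is tested only if the primary is significant, and that mean arterial pressure is reported descriptively. Systolic is an example: the article gives no ground for preferring it, and a rule requiring all measures, or a Bonferroni split, would also hold 5%. No proportion-at-target outcome needs to be added.

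The cost is a sentence in each section. The small downside is that a result on diastolic or mean arterial pressure alone could no longer be claimed as primary.

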### Statistical analysis

2.4

The analysis of all the data are conducted with the software of IBM SPSS Statistics for Windows, version 20 (IBM Corp, Armonk, NY). Afterwards, all the data acquired are represented through the appropriate characteristics, for example, standard deviation, and mean, median as well as percentage. And independent *t* tests and χ^2^-tests are respectively utilized to analyze the categorical variable and continuous variable. *P* value < .05 indicates that there is statistical significance.

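### The t test that falls to blood pressure, waist circumference and BMI makes no stated use of baseline; baseline-adjusted regression would be more precise at little cost

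*Protocol article*

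**What the plan says.** The Outcomes section of the protocol article states: "Primary result is blood pressure, while secondary results are treatment compliance, waist circumference, BMI". It does not say whether the quantity to be analysed is a follow-up value or a change from baseline.

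The Statistical analysis section covers all data with one sentence on testing: "independent *t* tests and χ^2^-tests are respectively utilized", applied in that order to categorical and then to continuous variables. Significance is set at P below .05. No section names a baseline covariate, a change score, ANCOVA or a repeated-measures model.

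The blank Table 1 in the Result section, titled as showing "the clinical outcomes between the two groups", has one column per arm and a P value. Its rows include systolic, diastolic and mean arterial pressure, waist circumference and BMI.

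On size, the section on inclusion and exclusion criteria says "there are 100 patients in each group". Allocation is by random-number table, and no stratification is mentioned.

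On measurement, the Nursing case management section gives the control arm "the monitor of blood pressure every 2 months". It gives the intervention arm, at six-monthly consultations, "the measurement of waist circumference and blood pressure, and the calculation of BMI". Blood pressure and weight are also checked at the intervention arm's home visits. No section describes a baseline assessment in either arm.

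**The concern.** Two things in the testing sentence need attention.

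First, read literally, it gives t tests to categorical variables and chi-square tests to continuous ones. This is almost certainly a slip, but it stands in the only sentence that fixes the analysis of the primary outcome.

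Second, with the pairing put right, the t test is the only named method that fits blood pressure, waist and BMI. A person's later value of such a measurement can be expected to relate to the earlier one. A plain comparison of follow-up values leaves that explained variation in the standard error. Precision is at stake: a wider interval and lower power than the same 200 patients could give. Type I error and bias are not.

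**Working it through.** **Inputs from the article.** 100 patients per arm; significance level 0.05; two-sample t test for continuous outcomes (after correcting the swapped pairing).

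**Assumed, because the article does not give them.** Two-sided testing; 80% power as the reference point; baseline to follow-up correlation r of 0.3, 0.5 or 0.7; equal SD at baseline and follow-up. An SD of 15 mmHg is used only to express results in mmHg. The article states no power, target difference or SD, so there is no figure of its own to reproduce.

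**Step 1: what the t test can detect.** Difference at 80% power = (1.960 + 0.842) × √(2/100) = 0.396 SD (normal approximation). At an SD of 15 this is 5.94 mmHg.

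**Step 2: ANCOVA against a t test on follow-up values.** The residual variance is (1 − r²) times the unadjusted variance, so the standard error and the detectable difference are multiplied by √(1 − r²). Power at the 0.396 SD effect is Φ(2.802/√(1 − r²) − 1.960). The equivalent unadjusted size per arm is 100/(1 − r²).

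| r | Variance factor | Reduction in SE | Detectable difference, SD units (mmHg at SD 15) | Power at 0.396 SD | Equivalent n per arm |
|---|---|---|---|---|---|
| 0 (t test) | 1.00 | 0% | 0.396 (5.94) | 80% | 100 |
| 0.3 | 0.91 | 4.6% | 0.378 (5.67) | 83.6% | 110 |
| 0.5 | 0.75 | 13.4% | 0.343 (5.15) | 89.9% | 133 |
| 0.7 | 0.51 | 28.6% | 0.283 (4.24) | 97.5% | 196 |

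**Step 3: if the t test were applied to change scores.** The variance of a change is 2(1 − r) times that of a single value: 1.4, 1.0 and 0.6 for the three correlations. Power at 0.396 SD would be 65.8%, 80.0% and 95.1%. The ANCOVA variance relative to this is (1 − r²)/[2(1 − r)] = (1 + r)/2, that is 0.65, 0.75 or 0.85. ANCOVA is more precise under this reading too, but the gain follows a different pattern.

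**Step 4: chance imbalance.** At an SD of 15, the baseline difference between arms has a standard error of 15 × √(2/100) = 2.1 mmHg, or a 95% range of about ±4.2 mmHg. On average r times that difference carries into an unadjusted follow-up comparison: about ±1.2, ±2.1 or ±2.9 mmHg for r = 0.3, 0.5 or 0.7. The t test's standard error already includes this variation. It is therefore the same cost as in step 2, not a second one.

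**Step 5: cost of the covariate.** One degree of freedom; the standard error rises by a factor of about √(1 + 1/196) = 1.0025.

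**The case against.** The strongest objection is that the unadjusted t test is a legitimate analysis of a randomised trial. That stands. A reader might infer that ignoring baseline biases the result, or that a chance imbalance passes whole into the estimate. Neither is so: only about r times the imbalance carries over, and the test's error rate already allows for it.

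A second objection is that a pre-randomisation reading cannot be taken for granted. This also stands. Eligibility asks for a diagnosis of hypertension, which is not a dated measurement. Blood pressure monitoring is described in both arms, but waist and BMI measurement only in the intervention arm; for controls it is implied only by the rows of Table 1. The benefit therefore depends on a baseline record that the article does not explicitly describe.

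Third, the article does not rule out a t test on change scores, which would use baseline. Step 3 covers that reading.

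Fourth, a reader might infer from Table 1 that no effect size could be obtained. That goes too far: means and standard deviations are promised, and with n per arm the unadjusted difference and its interval can be worked out.

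Fifth, the size rests on assumed correlations. At r = 0.3 the gain is small.

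Finally, it may be said that covariate adjustment belongs in an analysis plan. But the article is not silent here: it names the tests for all data. An analysis plan that followed it would carry out the less precise comparison.

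**Conclusion.** The point holds as one of efficiency. With the swapped pairing corrected, the named method for the primary outcome and for the continuous secondary outcomes is a two-sample t test with no stated use of baseline. It is valid but less precise than baseline adjustment.

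If follow-up values are compared, ANCOVA takes an effect with 80% power to about 84%, 90% or 98% at r = 0.3, 0.5 or 0.7. If change scores are compared, the variance falls to 0.65, 0.75 or 0.85 of theirs.

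These figures assume 100 analysed per arm, two-sided 5% testing, equal SDs and the stated correlations, none of which except the group size and the 5% level comes from the article. The documents do not support a claim that the planned test is biased, or that a baseline reading in both arms is already secured.

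**What to change.** 1. Correct the testing sentence so that continuous variables go with the t test (or its replacement) and categorical variables with the chi-square test.
2. Analyse each continuous outcome by linear regression of the value at one prespecified follow-up time point, common to both arms, on arm and the patient's own baseline value of that outcome.
3. Report the adjusted mean difference with its 95% confidence interval, and add it to Table 1, which is still blank.
4. State that blood pressure, waist circumference and BMI are recorded before randomisation in both arms.

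The cost is a change of wording and one degree of freedom (about 0.25% in the standard error). The method is standard linear regression, available in the SPSS package already named. The only possible extra data collection is the baseline record in item 4, if it is not already planned.
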